### Proposed trial outcome measures

All participants will be asked to complete follow-up questionnaires with a member of the research team at 3 and either 4, 5 or 6 months post-randomisation (see figure 3).

#### Smoking-related measures

Smoking status; 7-day point prevalence abstinence validated by exhaled CO <10 ppm, self-reported relapse following discharge from hospital, continuous abstinence, quit attempts, nicotine dependence as assessed by the Heaviness of Smoking Index,^29^ strength of urges to smoke,^30^ level of motivation to quit as assessed by the Motivation to Stop Smoking Questionnaire^31^ to assess how motivation changes over time and affects cessation outcomes, self-efficacy related to smoking cessation and use of e-cigarettes and NRT since discharge.

#### Mental and physical health measures

The 9-item Patient Health Questionnaire depression scale,^32^ the Generalised Anxiety Disorder 7-item scale^33^ and the quality-of-life scale (EuroQol- 5 Dimension (EQ-5D))^34^ will be included. Frequency of use of health services (health economic data) since discharge will also be collected.

We will review the suitability and definitions of the two core smoking-related outcome measures, as per current debate in the field,^35^ as follows: for 7-day point prevalence abstinence, we will review and potentially adjust downward the CO threshold of <10 ppm for biochemical validation, depending on the suitability of this approach for our patient population; for the multiple continuous abstinence outcome measures (1–6 months), we will review the availability and congruency of data and define one consistent secondary outcome measure accordingly.

### Sample size considerations

The feasibility study will be conducted across approximately 12 acute adult mental health inpatient wards of the participating eight Trusts. Based on combined monthly discharge figures of ~200 patients, of which we estimate conservatively that ~140 will be eligible to participate, a smoking prevalence of ~60%, and a conservative estimate of willingness of patients who smoke tobacco to take part of 20%, we will aim to recruit a minimum of 64 patients, who will be individually randomised, at a 1:1 ratio, to the SCEPTRE intervention or the control arm. A trial of this size^36^ will also allow a participation rate of 15% and completion rate of 80% to be estimated within a 95% CI of ±3% and ±10%, respectively.^37^

### Additional qualitative and quantitative measures of feasibility and acceptability

In line with recommendations for the reporting of protocols of pilot and feasibility trials,^38^ a range of quantitative and qualitative data for all participants (intervention and control arm) determining the acceptability and feasibility of intervention delivery and research procedures will be collected.

#### Recruitment and retention

All participants screened will be recorded in the eligibility screening log, with reasons for ineligibility and approach outcomes (outlined above). Retention rates will be monitored throughout the duration of the study, and the flow of participants will be detailed in a CONSORT diagram. If participants withdraw from the study, we will attempt to record their reported reasons where possible.

#### Compliance with the protocol

In addition to the interviews with MTSs (see above), compliance with the protocol and fidelity of intervention delivery will be optimised through monthly supervision sessions and monitored using self-assessment checklists and logs for MTSs delivering the intervention. The log will allow MTSs to record all contacts with participants, and the research team will judge the degree to which the intervention as designed has been delivered in practice. Any deviations from the protocol will be reported to YTU using a protocol deviation log.

#### Level of contamination and suitability of randomisation approach

The suitability of the individual randomisation approach will be assessed by using qualitative and quantitative data of control group participants who quit or reduced smoking at 3 and 4, 5, or 6 months post-randomisation. Quantitative investigation will take place in the context of follow-up, to identify and specify smoking behaviour change. Qualitative data will be obtained via interviews (outlined above) to investigate reasons for smoking behaviour change and identify potential (unintentional) links with the SCEPTRE intervention. Based on our findings, we will estimate the presence/extent of contamination in the control group and the need to change the unit of randomisation to clusters. If more than 30% of control participants appear to have changed aspects of their smoking behaviour due to factors directly related to our intervention, we will consider strategies to reduce contamination in the full randomised controlled trial (RCT), including the possibility of designing the full RCT as a cluster trial, with wards as the unit of randomisation.

### Data management

Each site will hold data according to the General Data Protection Regulations and the Data Protection Act 2018. All data will be stored on a secure password-protected server and archived for 10 years after study completion. Patients will be assigned a unique trial number, and this will be used on CRFs; patients will not be identified by their name in order to maintain confidentiality.

### Data analysis

A statistical analysis plan giving details of the planned analyses will be drafted before data collection has been completed and reviewed by the Programme Management Group (PMG) and PSC. A brief description of the planned analyses is given below.

The statistical analysis will be carried out by a statistician based in YTU, using Stata V.17 or later. The reporting of this trial will follow CONSORT guidelines for pilot and feasibility trials.^21^ A flow diagram will be produced, depicting the flow of patients through the trial. The number of patients screened, eligible, consenting and randomised will be summarised, with reasons for ineligibility and non-consent given where available. Baseline data will be summarised descriptively by randomised group, with no formal statistical comparisons being undertaken.^39^ Continuous variables will be summarised using descriptive statistics, while categorical variables will be summarised using counts and percentages. Descriptive statistics will summarise participant outcomes by randomised group and timepoint, including the amount of missing data. Relevant measures of recruitment and retention will be calculated and compared against the pilot progression criteria. The recruitment rate will be estimated and presented alongside a corresponding 95% CI. Measures of contamination and participant engagement with the multiple components of the intervention will be summarised descriptively.

Health economic analysis will be conducted as a preparatory step towards a comprehensive economic evaluation in the subsequent definitive RCT. Costs associated with the delivery of the SCEPTRE intervention and usual care will be estimated. All resources used in the provision of the intervention, such as the training for the MTSs, the staff time spent on delivering the intervention and the NRT and e-cigarettes dispensed, will be recorded alongside the trial. Data on the resources used in usual care through self-completed questionnaires at 3 and either 4, 5 or 6 months post-randomisation will be collected. A micro-costing approach, collecting detailed information about health service use, will be applied to generate estimated intervention costs for both arms by multiplying the quantity of each identified resource by its corresponding unit cost. We will pilot the data collection tools used to gather health economics data. We will test the feasibility and acceptability of the health service use questionnaire and the outcome measure instrument. We will examine the completion rates, identify any challenges or barriers to completion and make necessary modifications to the questionnaires for use in the full trial. The methods and findings will be summarised in a report that can be used to inform the design and conduct of the economic evaluation in the full trial stage.

Qualitative data analysis will be undertaken by group, for example, participants, MTSs, friends/family and Trust stakeholders. Data will be analysed using NVivo software (QSR International Pty, Melbourne, Australia). First, an inductive approach using thematic analysis will be used to identify nodes and subthemes in the data.^40^ Transcripts will be coded line by line by two researchers, with preliminary code names assigned to the data items and iteratively developed. Preliminary codes will be checked and discussed with a third researcher, experienced in qualitative research and the behaviour change wheel. Following this, a deductive approach will be used to chart subthemes to the APEASE criteria. The data will be presented and discussed in a wider research team meeting to refine and confirm the final interpretation.

### Trial management

A PMG has been established to oversee the day-to-day management (eg, protocol and ethics approvals, set-up, recruitment, data collection, data management) of the study, and is chaired by the chief investigator (CI). Membership includes co-CIs, co-investigators, research staff on the project and PPI representation. The role of the PMG is to monitor all aspects of the conduct and progress of the trial, ensure that the protocol is adhered to and take appropriate action to safeguard participants and the quality of the trial itself. Throughout the project, there will be regular videoconference contact supplemented by face-to-face meetings where required. Frequency of meetings will vary depending on the stage of the trial. The PMG, through the YTU, will provide feedback on trial progress to the PSC established to provide overall independent oversight for SCEPTRE on behalf of the Sponsor and Project Funder and to ensure that the project is conducted to the rigorous standards set out in the Department of Health’s Research Governance Framework for Health and Social Care and the Guidelines for Good Clinical Practice (GCP). Furthermore, the PMG through the YTU will provide feedback to the Data Monitoring and Ethics Committee (DMEC) established to monitor safety and efficacy data as well as quality and compliance data and ensure that the protocol is accurately followed, and the study is GCP compliant.

### Adverse events

All AEs occurring during the study observed by the investigator or reported by MTSs or participants will be recorded on the SCEPTRE Adverse Event Form for return to YTU. All serious adverse events (SAEs) will be entered onto the SAE reporting form and sent via REDCap or encrypted email to YTU within 24 hours of the investigator becoming aware of the event. Once received, causality and expectedness will be confirmed by the CI or a medical co-applicant or PSC member not acting as a site PI. Any change of condition or other follow-up information should be sent as soon as it is available or at least within 24 hours of the information becoming available. Events will be followed up until the event has resolved or a final outcome has been reached. SAEs that are deemed to be unexpected and related to the trial will be notified to the REC and sponsor within 15 days by YTU. All such events will be reported to the PSC and DMEC at their next meetings. Protocols and standard operating prodedures have been developed to identify and manage risks of suicide and harm to participants.

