#### Informed consent and data collection

Consent will be obtained in-person or remotely via telephone/video call. All participants will have received a copy of the participant information sheet at least 24 hours prior to obtaining consent. The consent form will also contain optional statements in relation to consent to interview for the qualitative aspect of the study.

Once participant eligibility has been confirmed and consent obtained, participants will be asked to complete a baseline questionnaire. If required, consent procedures and collection of baseline data can be separated into two visits dependent on participant preference. Data will be collected either using bespoke case report forms (CRFs) completed electronically via the secure web-based outcome data collection interface ‘REDCap’, over the telephone with a SCEPTRE researcher, or collected on paper CRFs returned via free post envelopes to York Trials Unit (YTU). All reporting of data collection will be undertaken in line with the CONSORT statement.^21^ The baseline assessment includes sociodemographic information as well as information on mental and physical health and smoking history and behaviour. Participants who self-report they have not smoked will be asked to provide an expired air carbon monoxide (CO) reading. We will ask participants for full contact details at baseline (including mobile phone number, email and address) and any contact preferences.

After the baseline assessment is completed, a member of the Trust’s research team will randomise participants to either the intervention or comparison group. All participants (intervention and control) will be followed up for the purposes of the study via self-completed questionnaires at 3 months and 4–6 months post-randomisation to accommodate a variable second follow-up period which allows us to extend the recruitment period without extending the duration of the study overall. During the follow-up, outcome measures to be collected include smoking-related measures and mental and physical health measures. While completing the follow-up questionnaires, participants who self-report that they have not smoked in the previous 7 days will be invited to undertake a CO measurement to validate their abstinence from tobacco. Participants who decline the invitation will be asked to provide a reason for declining, and this will be recorded on the questionnaire.

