### Intervention

#### Control arm: usual care

Participants randomised to the control arm will receive usual care. The local offer of smoking cessation support is variable across NHS mental health Trusts. Usual care in some Trusts may be comprehensive and include behavioural and pharmacological support during admission, whereas others may provide limited support (eg, access to nicotine replacement therapy (NRT)). Detailed information on what usual care entails on each inpatient ward will be collected. All participants will be provided with information on how to access Stop Smoking Services postdischarge.

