#### Intervention arm: SCEPTRE intervention package

Participants assigned to the intervention group will receive a 12-week intervention consisting of components aimed at promoting or maintaining smoking-related behaviour change among patients following discharge from a smoke-free mental health inpatient setting. See figure 2 for the SCEPTRE intervention pathway. The intervention development process was guided by the Behaviour Change Wheel model^22^ and theoretically underpinned by the Theoretical Domains Framework^23^ and the Behavioural Change Technique taxonomy.^24^ Intervention components were identified and further developed based on two systematic reviews and a Delphi-style consultation process with key stakeholders, including clinicians and patients.^16 25 26^ To ensure fit within the context of mental health services, refinement of the draft intervention was undertaken in collaboration with clinicians and experts in the field of tobacco control, and members of the SCEPTRE PPI panel. A more detailed description of the intervention and its development is provided elsewhere.^25^ The intervention will be delivered by trained mental health workers, named ‘My-Try Specialists’ (MTSs). The manualised intervention consists of several core and additional components outlined in table 1.

**Table 1 T1:** Summary of individual SCEPTRE intervention components

Intervention component	Core/additional	Aim	Frequency	Delivery
Pre-discharge reflection, evaluation and goal setting sessions	Core	Provide personalised and tailored support to assist participants in identifying and planning their smoking-related behaviour change goals. Discussions will also determine if participants want to use additional intervention components.	Participant-led; may include up to two sessions lasting up to 45 min	MTS to deliver
Provision of a bespoke and personalised resource folder: My-Try kit	Core	Kit including practical information and motivational content to support participants following discharge.	One kit provided pre-discharge	MTS to provide kit
Nicotine Replacement Therapy (NRT)/e-cigarette selection and advice	Core	To discuss preferences for NRT or e-cigarette support as well as practical advice in relation to using the products and obtaining a longer-term supply.	Discussed during pre-discharge reflection and evaluation session, and MTS will continue to provide advice in behavioural support calls	MTS to deliver

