Tailored behavioural support calls (via telephone or video call)	Core	Provide personalised and tailored support, assist the participant in maintaining positive change achieved during their smoke-free admission and achieving their behaviour change goals, and provide feedback and encouragement on participant’s progress.	Calls lasting 10–30 min for 12 weeks. On the first 5 days postdischarge, calls will be made daily, and weekly thereafter for the remaining eleven weeks	MTS to deliver
Smoke Free app	Additional	Provide additional support to participants, including its offer of 24/7 live smoking cessation advisor support	As required	MTS to deliver ‘onboarding’ session; smoking cessation advisors to provide advice via app
Text-based support	Additional	Personalised text messages to provide practical and motivational information to participants based on their individual goals (Appendix 2 shows example text messages)	15–30 text messages for 8–15 days dependent on goals	MTS to deliver

MTS, My-Try Specialist.

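### One of the three adverse-event reporting routes exists only in the intervention arm, and no matching enquiry is described for controls, so adverse-event counts by arm may not be comparable

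*Protocol article*

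**What the plan says.** The Adverse events section of the protocol article sets the rule for what is recorded: events during the study that are "observed by the investigator or reported by MTSs or participants". It names three routes: investigator observation, MTS report and participant report.

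The section on the SCEPTRE intervention package says that MTSs are the mental health workers who deliver the intervention. Table 1 gives the pre-discharge sessions as "Participant-led; may include up to two sessions lasting up to 45 min", and the support calls as follows: "On the first 5 days postdischarge, calls will be made daily, and weekly thereafter for the remaining eleven weeks". For the other arm, "Participants randomised to the control arm will receive usual care", with no MTS contact described.

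The follow-up common to both arms is in the section on informed consent and data collection: "All participants (intervention and control) will be followed up for the purposes of the study via self-completed questionnaires at 3 months and 4–6 months post-randomisation". Its content is given as smoking-related measures and mental and physical health measures. The list of mental and physical health measures adds frequency of health-service use since discharge. Adverse events are not named among the follow-up items.

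Under Trial management, a DMEC is "established to monitor safety and efficacy data as well as quality and compliance data".

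**The concern.** A rule that counts an event when someone hears of it is neutral between arms only if the chance of hearing is similar. Here one named reporter speaks regularly with intervention participants and, on the article's description, never with controls. If true event rates were equal, more events could still be recorded in the intervention arm.

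Timing differs as well. Intervention participants are called on each of the first five days after discharge. For controls, the first scheduled trial contact after discharge that the article describes is the 3-month questionnaire. The 24-hour reporting clock for serious events starts when the investigator becomes aware, so a control's event may enter the system later even if it is eventually captured.

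The DMEC would read counts by arm side by side whether or not a test is run. The study exists to try out recruitment, retention and data collection before a full trial, so an uneven capture process could be carried forward unnoticed. The limitations in the Discussion do not mention it.

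**Working it through.** The article states no adverse-event rate, detection rate or safety precision, so there is no figure of its own to reproduce. What can be checked is the contact schedule and, on assumed values, what it could do to the counts.

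**Step 1: scheduled contacts after randomisation.**

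| Contact | Intervention | Control | Source |
|---|---|---|---|
| Pre-discharge MTS sessions | up to 2 | 0 | Table 1 |
| Daily MTS calls | 5 | 0 | Table 1 |
| Weekly MTS calls | 11 | 0 | Table 1 |
| Follow-up questionnaires | 2 | 2 | Informed consent and data collection |
| Total | up to 20 | 2 | |

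Calls: 5 + 11 = 16. Intervention-only contacts: 2 + 16 = 18 at most. Unscheduled contacts are left out, as are those that reach only some participants (reminders to non-responders, in-person carbon monoxide readings, interviews).

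**Step 2: apparent rate ratio when true rates are equal.** The recorded rate is the true rate times the probability of detection, so the true rate cancels:

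apparent ratio = detection in intervention ÷ detection in control.

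Taking 80–90% and 50–70% as assumptions, over their full span:

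- smallest: 0.80 / 0.70 = 1.14
- largest: 0.90 / 0.50 = 1.80
- equal detection, for example 0.90 / 0.90 = 1.00

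**Step 3: the same in participants.** Expected number with a recorded event = 32 × true risk × detection. At an assumed true risk of 40% in both arms:

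- intervention at 90%: 32 × 0.40 × 0.90 = 11.5
- control at 70%: 32 × 0.40 × 0.70 = 9.0 (ratio 1.29)
- control at 50%: 32 × 0.40 × 0.50 = 6.4 (ratio 1.80)
- control at 90%: 11.5 (ratio 1.00)

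**Step 4: how far number of contacts alone could matter.** If each contact independently reveals an event with probability q, detection over k contacts is 1 − (1 − q)^k.

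- q = 0.1: 1 − 0.9² = 0.19 for k = 2; 1 − 0.9²⁰ = 0.88 for k = 20
- q = 0.2: 1 − 0.8² = 0.36; 1 − 0.8²⁰ = 0.99

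This exaggerates the gap for any event that also reaches the team by a route not tied to scheduled contacts. It shows direction, not size.

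**The case against.** The strongest reply is that two of the three routes, investigator observation and participant report, are open to both arms. The article does not say that MTSs ask about adverse events; their calls are described as smoking-behaviour support. Health-service use is collected from both arms at both follow-ups. Trust researchers visit participating wards, Trusts hold electronic records, and every participant's GP is told of the allocation, with a copy of the letter in the Trust notes. Serious events are reviewed one by one for causality and expectedness, which does not depend on a rate ratio. No direct comparison between groups is planned, and with 32 per arm none would be reliable. How events are elicited commonly sits in the full protocol, forms and operating procedures rather than in an article.

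Most of this stands, and it limits the point. It also rules out four stronger readings that a reader might infer:

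- That events are picked up essentially through MTS contacts. The rule names two other routes that cover both arms.
- That intervention-arm counts will be inflated. Events reported by MTSs are real events. What may be distorted is the contrast, chiefly through what is missed in controls, and the article gives no rates from which to predict it.
- That control readmissions would be visible only through the questionnaires. The ward and record links above make that doubtful, although no record search for adverse events is stated.
- That the data cannot inform safety monitoring in the full trial. Event types, relatedness and the working of the reporting process remain informative; only comparison by arm is weakened.

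The reply does not dispose of the point itself. This is not only a detail left to another document: the article states an ascertainment rule, and that rule names a reporter found in one arm only. Following it as written opens an unequal chance of detection. If the fuller documents contain a matched enquiry, one sentence would settle the matter.

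**Conclusion.** The point holds in a limited form. MTS report is one of three named routes and exists only in the intervention arm. It adds up to 18 scheduled contacts to the two follow-ups that both arms share, and no equivalent systematic enquiry is described for controls. Counts by arm may therefore not be comparable, mainly through under-detection or later detection in controls.

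The direction follows from the contact schedule. The size does not: the range of 1.14 to 1.80 rests wholly on the assumed detection probabilities and equal true rates, and the ratio could be near 1 for serious events that both arms' routes catch.

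The consequence is confined to by-arm safety summaries, DMEC review, and adoption of the same process in the full trial. The feasibility outcomes and progression criteria are not affected. This is a worthwhile, inexpensive improvement rather than a fault that undermines the study.

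**What to change.** 1. Ask the same structured adverse-event question of both arms at 3 months and at the 4–6 month follow-up. Use the health-service-use items already collected as a common source for hospital contacts.
2. Add a field to the adverse-event form for the source of each report (MTS, participant at follow-up, investigator, ward or record).
3. Base any by-arm summary on the sources common to both arms, and list events known only through MTSs separately. All events still go to the DMEC; only the comparative table is restricted.
4. State unequal ascertainment among the limitations.

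The cost is one questionnaire item, one form field and one extra table; the downside is a slightly longer questionnaire. The article describes the trial as ongoing, with recruitment open since January 2024. If it is too late to change the questionnaire, source labelling, the separate listing and the stated limitation can still be done, with the common question introduced in the full trial.
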